**Methods:**

Blood volume pulse (BVP; from which HR and HRV canl be derived) and EDA will be collected ambulatorily using the Empatica EmbracePlus from 40 youth (all genders; ages 8-17) undergoing six in-person exposure treatment sessions, as part of a multiple-baseline trial of exposure-based CBT for clinically impairing irritability. Clinical ratings of irritability will be conducted at baseline, weekly throughout treatment, and at 3-month and 6-month follow-ups via the Clinical Global Impressions Scale (CGI) and the Affective Reactivity Index (ARI; clinician-, parent-, and child-report). Multilevel modeling will be used to assess within- and between-person changes in physiological arousal and regulation throughout exposure-based CBT and to determine whether individual differences are predictive of treatment response.

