
### Study design

The data for the present study come from a randomized multiple baseline trial of exposure-based CBT. Each participant is randomized to 2, 4, or 6 weeks of baseline observation prior to treatment beginning. This design controls for the effects of time and regression towards the mean. Randomization is performed in blocks of 10 participants with a 1:1 within-block ratio. The assignment sequence was created via a computer-based random number generator. Clinicians conducting assessments (see below) are blinded to the trial phase from commencement of the baseline period, and the blind will not be broken for the entire cohort until the completion of the trial. The exposure-based CBT protocol will consist of twelve weekly sessions. Sessions are administered by two expert clinical psychologists. In-person exposure sessions (~30-45 minutes) will occur at weeks 5-10 in the protocol. Peripheral psychophysiological data will be collected during these six in-person exposure sessions. The main outcomes we plan to assess are changes in HR, HRV, and EDA over the course of exposure sessions and relations between changes in psychophysiological data and clinical symptoms. Clinical symptoms will be assessed weekly by clinician raters, including at mid-treatment, post-treatment, and 3- and 6-months post-treatment follow-up. Group supervision is conducted by the treatment developer and clinicians rate themselves on adherence after each session in order to improve adherence and minimize drift. Patients who request to discontinue or whose condition worsens (as determined by the clinical team and PI) may meet criteria for discontinuation. All participants are informed of their ability to discontinue at any time for any reason without the loss of benefits to which they are other entitled. For more extensive details regarding the intervention, please see Naim et al., 2021 and [69].

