### Data analysis

Extensive details of data management procedures can be found in Naim et al., 2021 and [69]. All participant data is de-identified using a numeric code to ensure confidentiality before, during, and after the trial. Only approved staff at the study site (National Institute of Mental Health) will have access to data. Estimates for HR, HRV, and EDA will be calculated as the session average for each individual across all sessions. Given the tendency of physiological data to be non-normally distributed, we will log-transform HR, HRV, and EDA data as necessary [55]. Questionnaire data will also be screened for normality and univariate outliers.

Multilevel models will be fit. Sessions (time; level 1) will be nested within person (level 2). Psychophysiological variables (HR, HRV, and EDA) from session 1 will be included at both levels 1 and 2 to account for the effects of individual differences at baseline on the intercept and slope, allowing us to test whether individual differences are predictive of treatment response within this model. Linear, quadratic, and cubic fits will be compared to determine the best-fitting model of change over treatment. First, we will sequentially fit models with psychophysiological indicators (HR, HRV, or EDA) from each of the five in-person exposure sessions defined as the outcome variable to assess change over time. Second, we will model severity of irritability based on the CGI as the outcome variable, and psychophysiological variables will be grand mean centered and entered as predictors at level 2 to assess the relation between change in psychophysiological parameters over time and irritability at post-treatment, 3-month follow-up, and 6-month follow-up. Missing data will be assessed for systematic loss and will be handled using full information maximum likelihood, which can handle both missing data and unequal time between measurement intervals [38]. We will use the Bonferroni-Holm method to correct for multiple comparisons.

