In addition to the dimensional models described above, wherein irritability and change in irritability are conceptualized continuously, we will also fit dichotomous treatment response models. Individuals will be classified as either high or low responders per the methodology described in [60]. High responders will be defined as those individuals who demonstrate a 50% or greater reduction in irritability based on the CGI at post-treatment assessment. Multilevel models will be fit as described above, with responder status as the outcome variable.

Should our primary hypothesis testing reveal changes in arousal (HR/EDA) and regulation (HRV) over the course of in-person exposure sessions, we will perform post hoc exploratory analyses to investigate the temporal relationship between psychophysiology and change in symptoms over the course of treatment using cross-lagged panel modeling. To capture weekly variation in symptoms, we will use the CGI rated at each exposure session. A random intercept cross-lagged panel model (RI-CLPM) will be specified in R using the lavaan package [82]. Four components will be specified: (1) a between component, consisting of random intercepts; (2) within-person fluctuations; (3) the lagged regressions between within-person components; and (4) covariances of the within and between components [68]. Within-person variables will be mean-centered.

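### The CGI and responder analyses leave out the randomised baseline phase, so they cannot tell physiology that tracks untreated course from physiology that tracks response to CBT.

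*Protocol article*

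**What the plan says.** The Study design section states: "Each participant is randomized to 2, 4, or 6 weeks of baseline observation prior to treatment beginning". It credits this arrangement directly: "This design controls for the effects of time and regression towards the mean". All children then receive twelve weekly sessions. In-person exposures fall in weeks 5 to 10, and "Peripheral psychophysiological data will be collected during these six in-person exposure sessions".

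The Data analysis section sets out four analyses:

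- HR, HRV or EDA over the exposure sessions. The structure is given as "Sessions (time; level 1) will be nested within person (level 2"), and session-1 physiology enters at both levels.
- CGI severity at post-treatment, 3 months and 6 months, with physiology as a level-2 predictor.
- Responder status, defined by a "50% or greater reduction in irritability based on the CGI at post-treatment assessment". The rating from which the reduction is taken is not named.
- A conditional, exploratory random-intercept cross-lagged model using the CGI at the exposure sessions.

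Of including session-1 physiology, the section says that it does so "allowing us to test whether individual differences are predictive of treatment response within this model".

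The two descriptions of rating frequency differ. The abstract has "Clinical ratings of irritability will be conducted at baseline, weekly throughout treatment, and at 3-month and 6-month follow-ups". Study design has "Clinical symptoms will be assessed weekly by clinician raters", and the time points it then lists are mid-treatment, post-treatment and follow-up.

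**The concern.** A multiple-baseline design controls for time and regression to the mean only if the analysis contrasts the baseline phase with the treatment phase. None of the stated models does. The word baseline in the model description refers to physiology at session 1, which is recorded during treatment and not in the randomised baseline.

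The symptom models are therefore a single-group follow-up. Physiology that marks children who would have improved anyway, and physiology that marks children whom CBT helps, produce the same association. The Summary and Hypotheses section sets out to find mechanisms of treatment efficacy and to predict individual treatment response, so this distinction decides how a positive result may be read.

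**Working it through.** **1. The plan's own figures.** Sample size and power analysis gives power of 52.7%, 29.7% and 31.0% at n = 40 for hypotheses 1, 2 and 4. These cannot be rebuilt, because no effect size or variance from the seven pilot participants is given. The point does not depend on them.

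**2. Does any stated model use the baseline phase?**

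| Analysis | CGI ratings used | Phase term | Baseline length |
|---|---|---|---|
| Physiology over sessions | none | no | no |
| CGI severity | post-treatment, 3 and 6 months | no | no |
| Responder | post-treatment, against an unnamed reference | no | no |
| Cross-lagged | exposure sessions | no | no |

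**3. Size, simple version.** Assume that a marker has no relation to the effect of CBT but correlates r with post-treatment CGI-S through untreated course alone. The chance of significance is approximately 1 − Φ(z − atanh(r)·√(n − 3)), with n = 40 and √37 = 6.083. At unadjusted two-sided 0.05, z = 1.96:

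- r = 0.2: atanh = 0.2027; 0.2027 × 6.083 = 1.233; 1 − Φ(0.727) = 23%
- r = 0.3: atanh = 0.3095; 0.3095 × 6.083 = 1.883; 1 − Φ(0.077) = 47%
- r = 0.4: atanh = 0.4236; 0.4236 × 6.083 = 2.577; 1 − Φ(−0.617) = 73%

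The plan applies Bonferroni-Holm without giving the family size. If the family were three markers (assumed), the strictest step is 0.05/3, so z = 2.394, and the figures become 12%, 31% and 57%. Correction lowers the rate but does not remove the confounding.

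**4. Size, simulation.** Assumptions, none from the documents: weekly CGI in both phases; each child has a linear natural slope with SD 0.08 points a week that runs through both phases; residual SD 0.6; treatment slope change −0.12 a week; CGI treated as continuous. The marker correlates r with the natural slope and is unrelated to the treatment effect. The treatment-phase-only analysis regresses the treatment-phase CGI slope on the marker, as a stand-in for the planned models. The phase contrast regresses the change in slope at treatment start on the marker. There were 4,000 runs per setting, and the entries are the chance of calling the marker predictive at 0.05:

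| r | Treatment phase only | Phase contrast |
|---|---|---|
| 0 | 5.4% | 5.0% |
| 0.3 | 37% | 5.3% |
| 0.4 | 62% | 4.6% |
| 0.5 | 82% | 4.6% |
| 0.6 | 95% | 4.5% |

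If the treatment effect also varies between children (SD 0.08 a week, assumed), the treatment-phase-only rates at r = 0.3 and 0.4 fall to about 23% and 38%. Here r is a correlation with the natural slope. In step 3 it is a correlation with post-treatment CGI-S, so the two sets of figures are not interchangeable.

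**5. What the phase contrast can detect.** Under the same settings with treatment-effect SD 0.08, a marker truly correlated 0.3, 0.4 or 0.5 with the treatment effect is found in about 12%, 19% or 26% of trials.

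**6. Timing.** Treatment ends at trial week 2 + 12 = 14, 4 + 12 = 16 or 6 + 12 = 18. If untreated CGI-S fell 0.05 points a week (assumed), the four-week gap between the shortest and longest baseline is worth 4 × 0.05 = 0.2 points from entry.

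**The case against.** Several counter-arguments have force.

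- **Baseline ratings may be sparse.** Weekly ratings within the baseline phase are not clearly documented. Blinding raters to phase from the start of the baseline period suggests that some are taken there, but no number is given. With a single rating, a baseline slope cannot be fitted. This stands, and it rules out treating the slope contrast as certainly available.
- **A phase contrast is not clean.** Physiology is first recorded in treatment week 5, so it may already reflect four weeks of CBT. The contrast also assumes linear natural course, whereas regression to the mean tends to come early. The near-5% column in step 4 owes its flatness to that assumption. Power is low (step 5). A reader might infer that the interaction should be the only basis for any symptom claim; these limits make that too strict.
- **Error rates are stipulated.** A reader might infer that a prognostic marker will be reported as a predictor of response. The documents give no correlation between physiology and untreated course, so this stays conditional.
- **Staggered end dates.** Baseline length is randomised, hence balanced in expectation against stable characteristics, and 0.2 assumed points is small. A reader might see a bias here; the documents do not show one. Adjustment is cheap tidying.
- **Association and caveats.** Hypothesis 4 speaks of association, and the Discussion concedes that strong causal inference is not possible. Both are fair, but neither withdraws the treatment-response reading that Data analysis attaches to session-1 differences, and a general caveat does not separate prognosis from response.
- **Condensed article.** Covariates are often left to an SAP. Here, however, the article fixes levels, predictors and outcome times and states the inference, so the mismatch is in the text itself.

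**Conclusion.** The point holds in a limited form. The stated CGI and responder models make no use of the randomised baseline, and so cannot support the claim that they test prediction of treatment response, as opposed to outcome during treatment. That follows from the text and needs no assumption. The size is unknown. Steps 3 and 4 show that it could be large at n = 40 if physiology tracks untreated course moderately, but every percentage rests on assumed correlations and unadjusted alpha 0.05, except the Holm variant shown.

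The point concerns the symptom models only. Hypotheses 1 to 3, on change in HRV, HR and EDA, have no untreated comparator whatever is done with the CGI, because physiology is not recorded in the baseline phase. Untreated here means before CBT, since existing medication may continue. The change should be made: it affects the central interpretation.

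**What to change.** 1. In the CGI-S and responder models, include the child's last baseline-phase CGI-S and the randomised baseline length. State that the 50% reduction is measured from that rating. This handles starting severity and elapsed time; it does not by itself separate prognosis from response.
2. Confirm how many CGI-S ratings are taken within each baseline length, and reconcile the abstract with Study design.
3. If the ratings are frequent enough, add a supporting model of all CGI-S ratings from the start of baseline: trial week, a change in slope at the child's randomised treatment start, and physiology interacting with both. State its limits: linear natural course, physiology first measured in treatment week 5, low power with 40 children.
4. Unless that contrast supports more, describe results as predictors of outcome during treatment, and reword the treatment-response sentence in Data analysis to match.

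Cost: analysis wording and a little extra modelling, using assignments and at least one pre-treatment rating that the trial already has. The slope model depends on item 2. The price is a less favourable and less precise claim.

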### Summary and Hypotheses

Psychophysiology has played a role in distinguishing the phenotype of clinically impairing irritability, whereby youth with clinically impairing irritability report more arousal during an affective task [81]. As highlighted above, elevated arousal and decreased regulation at the level of the ANS are broadly implicated in psychopathology, including irritability. Probing variation in arousal and regulation as measured by HR, HRV, and EDA has the potential to elucidate mechanisms underlying exposure-based treatment based on principles of extinction, prediction of individual treatment response, and evaluation of treatment efficacy.

The aim of this proposed study is to assess in vivo psychophysiology—HRV, HR, and EDA—across in-person exposure-based CBT sessions for youth with clinically impairing irritability. The trial will include youth requiring treatment for a primary concern of severe and impairing irritability in multiple domains that cut across DSM-5 diagnostic categories. Our goal is to identify potential putative psychophysiological mechanisms of treatment efficacy. We consider three psychophysiological signals, as they are differentially regulated and represent variant psychological manifestations [62].

Our primary hypotheses are the following: (1) HRV will show an increase over time across sessions, reflecting improved regulation; (2) HR will show a reduction over time between sessions, reflecting decreased arousal; (3) EDA will show a reduction over time between sessions, also reflecting decreased arousal; and (4) these changes will each be associated with measurable improvement in symptoms over the course of treatment.

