Post hoc exploratory analyses will probe causality, as indicated by temporal associations. That is, we will assess whether changes in psychophysiology precede and predict changes in symptoms over the course of treatment or vice versa using cross-lagged panel models. Of note, a consideration that affects most hypotheses is that blunted HR and EDA at initial exposure may be maladaptive [77, 83], possibly indicative of avoidance. Higher HR and EDA at the beginning of treatment may demonstrate both sufficient engagement in exposures and sufficiency of exposures to evoke a level of physiological arousal equivalent to that experienced in a naturalistic setting. Additionally, increased HR/EDA and decreased HRV at initial in vivo exposure may reflect a greater ability of youth to engage in context-appropriate responses and, thus, more likely to have better treatment outcomes. At the same time, higher HRV could reflect active avoidance [9]. Accordingly, we will adjust our models using formal comparison by information criteria to account for potential nonlinear changes caused by initial avoidance.

Aberrant emotions and behaviors are subserved by measurable physiological processes [24]; studying them could provide novel mechanistic insights into the psychopathology of irritability in youth. By examining psychophysiology during exposure sessions, we can probe the dynamic processes underlying adaptation to challenge in real-time [55], and how they vary within and between individuals over the course of treatment.

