### Sample size and power analysis

The sample size for the overarching multiple baseline trial of exposure-based CBT was previously determined by [73] using pilot treatment data [47] and established a priori as n = 40. Based on preliminary data from n = 7 participants, n = 40 achieves power = 52.7% at alpha=0.05 for hypothesis 1, power = 29.7% at alpha = 0.05 for hypothesis 2, and power = 31.0% at alpha = 0.05 for hypothesis 4. However, given that these power analyses were based on a small pilot sample, they may be unreliable. A similarly designed study of changes in HR and HRV over the course of CBT identified significant effects in a sample of n = 43 [25]. Data from the present study will be used to inform the design of higher-powered studies to further explore the mechanistic predictors and underpinnings of this novel treatment.

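### Hypotheses 1–3 are directional, but the time curve is chosen on the same data and no fixed quantity decides whether a signal rose or fell, so the nominal 5% error rate is not assured

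*Protocol article*

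**What the plan says.** Summary and Hypotheses lists three primary hypotheses about the signals, each with a direction: "HRV will show an increase over time across sessions, reflecting improved regulation"; "HR will show a reduction over time between sessions, reflecting decreased arousal"; "EDA will show a reduction over time between sessions, also reflecting decreased arousal".

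The same section expects that avoidance at the first exposures may bend the time course, and responds: "we will adjust our models using formal comparison by information criteria to account for potential nonlinear changes caused by initial avoidance". Data analysis closes the candidate set: "Linear, quadratic, and cubic fits will be compared to determine the best-fitting model of change over treatment". The chosen model then has each signal "defined as the outcome variable to assess change over time".

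The article does not say whether the criterion is AIC or BIC, how time is coded, which quantity decides each hypothesis, or whether tests are one- or two-sided. Bonferroni-Holm is named for multiple comparisons, but nothing extends it to the choice of curve. Later in Data analysis, a finding of change in the signals triggers the exploratory cross-lagged models.

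Two related statements affect any repair. Study design has six in-person exposure sessions with recordings, while Data analysis speaks of five. Data analysis also enters the session-1 physiology as a predictor at both levels.

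**The concern.** A directional hypothesis needs one number whose sign and test settle it. A straight line supplies one, the slope. A quadratic or cubic does not: the slope differs at every session, and the first-order coefficient is only the slope at whichever session is coded zero. The article foresees curved models, so this case is likely to arise.

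There is also an error-rate question. If the data choose the curve and the hypothesis is then judged in the chosen model as though it had been fixed, the p-value ignores the selection. Holm adjusts across the p-values it is given and cannot repair one that is already too small. At stake are the per-signal error rate of three primary hypotheses, the comparability of the three conclusions, and the trigger for the cross-lagged analyses.

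**Working it through.** **1. The plan's own figures.** Sample size and power analysis states "n = 40 achieves power = 52.7% at alpha=0.05 for hypothesis 1", "power = 29.7% at alpha = 0.05 for hypothesis 2" and 31.0% for hypothesis 4, with no figure for hypothesis 3. These cannot be reproduced, because no effect size, variance or sidedness is given. If a one-sample two-sided test is assumed, d = (1.960 + z(power))/√40:

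- Hypothesis 1: (1.960 + 0.068)/6.325 = 0.32
- Hypothesis 2: (1.960 − 0.533)/6.325 = 0.23
- Hypothesis 4: (1.960 − 0.496)/6.325 = 0.23

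This shows scale only. It does not reveal which test of change was powered.

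**2. Direction in a curved model (illustration).** Take y = 2t − 0.6t², with t = 0 to 5 for six sessions. The values are 0, 1.4, 1.6, 0.6, −1.6, −5.

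- Slope at session 1: 2 − 1.2 × 0 = +2
- Slope at session 6: 2 − 1.2 × 5 = −4
- Last minus first: −5 − 0 = −5
- Best straight line: over t = 0 to 5 the regression of t² on t has slope 5, so 2 − 0.6 × 5 = −1

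The same curve is a rise by the first quantity and a fall by the other three.

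**3. Precision of the session-1 coefficient.** For t = 0 to 5 the centred sums are Σt² = 17.5, Σ(t²)² = 474.83 and cross-product 87.5. So r² = 87.5²/(17.5 × 474.83) = 0.921, and the standard error grows by 1/√(1 − 0.921) ≈ 3.6 when the quadratic term is added. The cubic factor is 8.0. Both factors apply only if time zero is session 1.

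**4. False-positive rate under no change.** From the article: n = 40, six or five sessions, three candidate curves, alpha 0.05. Assumed: balanced data, random intercept only, no session-1 covariate, two-sided tests, maximum-likelihood AIC or BIC. There were 10,000 null trials per setting, with a Monte Carlo standard error of 0.2 to 0.4 points.

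AIC picks a curved model in about 22% of null trials (six sessions: 13.6% quadratic + 8.3% cubic), and BIC in about 2%.

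| Test in the selected model | AIC, 6 / 5 sessions | BIC, 6 / 5 sessions |
|---|---|---|
| First-order coefficient, zero at session 1 | 11.7% / 12.0% | 6.7% / 7.2% |
| Joint test of the selected time terms | 8.9% / 9.4% | 6.7% / 7.2% |
| Any time term significant | 15.0% / 15.5% | 6.8% / 7.5% |
| Orthogonal linear trend | 4.8% / 5.3% | 4.8% / 5.3% |

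A linear slope fixed in advance, with no selection, gives 4.8% / 5.2%.

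Two further settings:

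- With time centred mid-treatment, the first-order coefficient gives about 8.5–8.8% under AIC and 5.3–5.5% under BIC.
- The last-minus-first contrast from the selected model (six sessions, 20,000 trials) gives 5.9% under AIC and 4.9% under BIC.

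Across repeated runs, the first-order and joint tests fall at about 8–13% under AIC and 5–7% under BIC.

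**The case against.** The strongest reply is that this is a condensed article. The time coding, the contrast and the choice between AIC and BIC are the kind of detail an analysis plan supplies, and that plan is not shown. Nowhere does the article say that a session-1-coded coefficient will decide the hypotheses. The selection is also planned: the method is named, the candidates are limited to three, and a substantive reason is given. The simulated model is simpler than the planned one, since it lacks random slopes, missing sessions and the session-1 predictor. The study admits low power, and the cross-lagged step is labelled exploratory.

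Much of this stands. A reader might infer that the error rate is about 12%. The documents do not support that, because the figure needs AIC, session-1 coding and the raw first-order coefficient, and none of these is stated. Nor is it fair to call the selection unplanned, or to treat different curves for HR, HRV and EDA as a fault in themselves, since the article regards the signals as differentially regulated. A reader might also expect a real steady change often to be missed. On average that effect is small: with a true linear effect sized for about 53% power, AIC selection gave 51%.

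What the reply does not remove is that the article goes beyond silence. It states a data-driven rule for the model in which directional primary hypotheses are judged, and under that rule the direction has no single meaning once a curve is chosen.

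**Conclusion.** The point holds in a conditional form. Hypotheses 1–3 have no single deciding quantity once a quadratic or cubic model is selected, and the nominal 5% per signal is not assured. Depending on choices the article does not state, the rate runs from about 5% (a linear trend kept whatever the curve) to about 15% (any significant time term under AIC). These figures rest on the simplified balanced, random-intercept simulation and show the possible spread; they do not predict the rate of the planned model. The five-versus-six conflict does not alter the conclusion, since both were simulated. The matter deserves correction because the hypotheses are primary and the repair is cheap, but it does not undermine the design.

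**What to change.** First reconcile five versus six sessions between Study design and Data analysis, and state whether session 1 is an outcome or only a predictor. If it is only a predictor, a contrast starting at session 1 is not a direct output of the model, and the first modelled session is the next one.

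Then, before the physiological data are analysed, name one test of change for HR, HRV and EDA, with its sidedness, to be applied whatever curve is selected. It can be either the linear trend or the model-estimated difference between the last and first modelled exposure sessions. Name the information criterion, and use the curve comparison only to describe shape, reported as exploratory.

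The cost is wording, plus settling the session question. There is a small downside: a single linear trend can understate a rise followed by a fall, which the exploratory shape comparison would still show.

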### Materials and measures

#### Questionnaires and clinical assessments

Assessments are performed by trained and liscensed masters- or doctoral-level clinicians who are blinded to the treatment. Clinical outcome measures will include the Clinician Affective Reactivity Index (CL-ARI [33];) to measure changes in irritability, and the Clinical Global Impressions-Severity (CGI-S) and CGI-Improvement (CGI-I) scales to measure overall illness severity and improvement [14]. Child- and parent-reported irritability will also be assessed using the child and parent-report versions of the ARI. The CGI-S will be the primary indicator of illness severity in analyses. Secondary analyses may also explore patterns of change and predictors of improvement based on the ARI, which includes not only the clinician but also the parent and child reports.

The CGI-S assesses the severity of psychopathology (here, irritability) on a 1-7 Likert scale where 1 = normal, not at all ill, and 7 = among the most extremely ill patients [14]. The CGI-I assesses change from the start of treatment on the same 7-point Likert scale, where 1 = very much improved and 7 = very much worse.

The CL-ARI is a reliable and valid measure comprising three subscales for temper outbursts, irritable mood between outbursts, and impairment [33]. Items are scored on Likert scales where higher scores indicate more severe, longer duration, and greater frequency of outbursts, mood, and impairment. Similarly, parent- and child-report versions of the ARI (six symptom items and one impairment item) show excellent internal consistency across samples (A [89, 91].).

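### Read literally, the 50% responder cut on the CGI ignores that the scale starts at 1, so exact half-way moves to normal (3→2, 5→3, 7→4) count as low response

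*Protocol article*

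**What the plan says.** The Data analysis section of the protocol article adds a set of dichotomous models to the continuous ones. Participants are split into high and low responders by a method attributed to a cited study (reference 60). A high responder is someone with a "50% or greater reduction in irritability based on the CGI at post-treatment assessment". The split is then used as an endpoint: "Multilevel models will be fit as described above, with responder status as the outcome variable".

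The section on questionnaires and clinical assessments describes two CGI scales. The CGI-S rates severity "on a 1-7 Likert scale where 1 = normal, not at all ill, and 7 = among the most extremely ill patients". Of the other it says: "The CGI-I assesses change from the start of treatment on the same 7-point Likert scale". It also states: "The CGI-S will be the primary indicator of illness severity in analyses". The responder sentence itself says only CGI, without naming the scale.

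**The concern.** A percentage reduction measures relative improvement only when zero means no illness. On the CGI-S, no illness is a score of 1. Complete recovery from 5 is a fall of 4 points, or 4/5 = 80% of the raw score; complete recovery from 3 is 2/3 = 67%. Half the raw score is therefore more than half the illness, and the gap widens as the baseline falls.

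If the rule is applied as worded, some children who have covered half the distance to normal enter the responder models as low responders. Those models ask whether physiology is related to treatment response, so the definition of response should mean what its percentage suggests. It should also be fixed before anyone is classified, because a cut changed after results are seen would look data-driven.

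**Working it through.** **Inputs.** The cut (50% or greater) and its timing (post-treatment) come from Data analysis. The range 1 to 7 with 1 = normal comes from the section on questionnaires and clinical assessments. The sample size of 40 comes from the sample size section. I assume that ratings are whole numbers and that the CGI-S is meant, since a percentage reduction from baseline has no meaning on the CGI-I, which is already a change rating.

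**The plan's own figure.** The 50% is a definition, so there is nothing to reproduce. The article gives no responder rate. Nothing in the sample size section says that its power figures (52.7%, 29.7% and 31.0%) rest on this cut.

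**Formulas.** Let b be the baseline score and s the post-treatment score.

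- Literal rule: (b − s)/b ≥ 0.5, which is s ≤ b/2.
- Floor-adjusted rule: (b − s)/(b − 1) ≥ 0.5, which is s ≤ (b + 1)/2.
- Share of the distance to normal covered: (b − s)/(b − 1).

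**Highest post-treatment score that still qualifies:**

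| Baseline b | Literal: s | Share of distance to normal | Adjusted: s | Share of distance to normal |
|---|---|---|---|---|
| 7 | 3 | 4/6 = 66.7% | 4 | 3/6 = 50% |
| 6 | 3 | 3/5 = 60% | 3 | 3/5 = 60% |
| 5 | 2 | 3/4 = 75% | 3 | 2/4 = 50% |
| 4 | 2 | 2/3 = 66.7% | 2 | 2/3 = 66.7% |
| 3 | 1 | 2/2 = 100% | 2 | 1/2 = 50% |
| 2 | 1 | 1/1 = 100% | 1 | 1/1 = 100% |

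**Which children change class.** With whole-number scores, an exact half-way move exists only at odd baselines, and the literal rule fails each one:

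- 7→4: 3/7 = 42.9% of the raw score
- 5→3: 2/5 = 40.0%
- 3→2: 1/3 = 33.3%

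At baselines 2, 4 and 6 the two rules agree on every child.

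**Floor and rounding separated.** If scores were continuous, halving the raw score would cover 0.5b/(b − 1) of the distance to normal: 58.3% at 7, 60% at 6, 62.5% at 5, 66.7% at 4 and 75% at 3. That excess over 50% comes from the floor alone. The rest of the unevenness in the literal column comes from whole-number scoring, and the adjusted rule does not remove that part.

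**Size in the trial.** The number reclassified equals the number of children moving 7→4, 5→3 or 3→2. It is zero if all start at even scores. With all 40 assessed, each such child moves the responder rate by 1/40 = 2.5 percentage points.

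**The case against.** **The raw formula is only the literal reading.** The sentence speaks of a reduction in irritability based on the CGI and refers the classification to a cited study that is not at hand. A floor adjustment there cannot be excluded, and a condensed article may leave the formula to a fuller plan. This stands as a limit on certainty. It does not clear the sentence, which sets a cut on a named instrument and states no adjustment.

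**Half-way to normal is not the plan's own standard.** The article never says that response means covering half the distance to normal, and a stricter cut could be chosen deliberately. That is fair. But the article gives no reason for a cut that works out at 60%, 75% or 100% according to baseline while being labelled 50%.

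**Uneven treatment by baseline survives the fix.** A reader might take the contrast between 5→3 (low) and 4→2 or 6→3 (high) as proof of the floor problem. It is not: any proportional rule on whole numbers produces such contrasts. After adjustment 5→3 is high at 50%, while 6→4, also two points, is low at 2/5 = 40%.

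**A reader might infer bias in the predictor comparison**, because the Background links arousal to severity of irritability. The documents do not support that step. The literal rule's required share at baselines 4 to 7 is 66.7%, 75%, 60% and 66.7%, which does not rise or fall steadily with severity. Nothing in the article links physiology to odd rather than even scores.

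**A reader might also connect the CGI-I**, which is anchored to the start of treatment, with assessors who "are blinded to the trial phase from commencement of the baseline period". That is a separate matter. The CGI-S is named as the primary severity measure, and re-anchoring the CGI-I would not change the responder cut.

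**The analysis is supplementary.** The four primary hypotheses do not use responder status. This stands and limits the weight of the point.

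**Conclusion.** The point holds in a limited form. Taken literally on the CGI-S, the responder rule asks for 60% to 100% of the distance to normal at baselines 3 to 7. It classes the exact half-way moves 3→2, 5→3 and 7→4 as low response. Baselines 4 and 6 are unaffected.

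This rests on three assumptions: the CGI-S is meant, the percentage is of the raw score, and ratings are whole numbers. How many children are affected cannot be known without a baseline distribution. Entry requires marked impairment, so it is doubtful that many start at 3. No direction or size of bias can be claimed. The continuous CGI models are unaffected. The rule is worth correcting because it is fixed badly as written and the remedy costs almost nothing.

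**What to change.** Replace the responder sentence with one that:

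- names the CGI-S;
- defines a high responder as (baseline − post)/(baseline − 1) ≥ 50%;
- takes baseline as the last rating before treatment starts, and post as the post-treatment rating.

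Keep the raw-score version as a sensitivity analysis, and make the change before responders are classified.

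The cost is one sentence and no new data. There are two downsides. The responder rate may be less comparable with the cited method, which the sensitivity analysis partly covers. Some dependence on baseline also remains from whole-number scoring: the required share still runs from 50% to 67% for baselines 3 to 7, against 60% to 100% under the literal rule.
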